## Outcomes

6

### Primary Efficacy Endpoint

6.1

The key primary efficacy endpoint is a standard win ratio composed of time to occurrence of all‐cause death and the number of non‐fatal cardiovascular hospitalizations from randomization to Week 84. These events will be identified using multiple verified data sources, including EHRs, discharge summaries, and official death certificates, and will undergo centralized review by the data management team to ensure accuracy and completeness across sites. The objectivity of these outcomes, combined with centralized validation procedures, minimizes the potential for ascertainment bias.

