**Methods:**

This is an open‐label randomized and decentralized clinical trial describing the design and methodology of the TAMIS program, which will assess its impact on community‐dwelling diabetic subjects with uncontrolled HBA1c and uncontrolled LDL‐C and/or blood pressure. Individuals will be randomized to usual care or remote care and followed for 84 weeks. Remote monitoring offers a practical response to the limited capacity of LMIC health systems to ensure sustained follow‐up and continuity of care for chronic conditions. The primary endpoint is a win‐ratio of hierarchical events, including all‐cause deaths and the frequency of all‐cause hospitalizations. The secondary endpoints include control of HbA1c, LDL‐C and blood pressure according to clinical guidelines, as well as patient‐reported outcomes and clinical parameters, including blood pressure, glycemic control, and LDL cholesterol levels. Subgroup analyses will explore the impact of demographics and clinical characteristics on treatment outcomes. Overall, the study aims to improve health care delivery, enhance patient education, and foster collaboration between patients and health care providers to mitigate the growing burden of cardiovascular diseases in LMICs.

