## Sample Size Calculation

7

Given that a comprehensive multifactorial intervention targeting intensive cardiovascular risk factor control has been associated with significant reductions in cardiovascular mortality (−57%), cardiovascular events (−59%), and hospitalizations due to heart failure (HF) in patients with diabetes [1], this study was designed using a standard win ratio test. The win ratio test incorporates both all‐cause mortality and all‐cause hospitalizations, using component‐wise hazard ratios (HRs) as effect size estimators.

For the sample size estimation, predefined hazard ratios (HR 0.90 for all‐cause death and HR 0.70 for all‐cause hospitalization) were used, targeting 90% statistical power with a two‐sided *α* = 0.05% and 5% expected attrition. Sensitivity analyses explored plausible variations in baseline event rates and component HRs to confirm robustness of the win‐ratio and power assumptions. A total of 838 participants (419 per treatment arm) will provide adequate power under these scenarios. Sample size calculations were performed in R (v1.2) using the WR package, as described by Mao et al. and Yu et al. [14, 15]. Supporting Information Material 4 summarizes the simulation scenarios and corresponding sample size estimates.

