### Statistical Methods

9.4

All continuous variables will be presented as median and interquartile range (IQR), while categorical variables will be reported as absolute (n) and relative frequency (%).

Descriptive statistics (mean ± standard deviation, median and IQRs) will be generated for each treatment group to summarize demographic and baseline characteristics. Between‐groups comparisons will be conducted within the Intention‐to‐Treat (ITT) population to ensure that the randomization process successfully achieved balance between groups. Differences in baseline characteristics between treatment groups will be tested using a chi‐square test for categorical variables and a two‐tailed *t*‐test with treatment as a factor for continuous variables. These preliminary analyses will serve as an initial assessment of the adequacy of randomization.

The primary endpoint analysis will be performed using a win‐ratio test, which combines time to all‐cause death and the frequency of nonfatal hospitalizations. The win ratio test will follow the original methodology described by Pocock et al. [16]. Beyond hierarchical endpoint evaluation, this approach allows for the integration of multiple endpoint types. Treatment differences will be tested at an alpha level of 0.05, with a sequential procedure for controlling type 1 error. Additional covariate adjustments for time‐sensitive analyses will be performed using a Cox proportional hazards model, incorporating the randomization stratification factor. The HR for treatment groups will be reported along with the 95% confidence interval (CI).

The secondary endpoint analysis will be performed using Kaplan‐Meier survival curves, evaluating time‐to‐event data for each secondary efficacy endpoint. The log‐rank test used for the primary endpoint analysis will also be applied to secondary endpoints. Treatment differences will be tested at an alpha level of 0.05, employing a sequential procedure for type 1 error correction. Covariate adjustments for time‐dependent analyses will again be performed using the Cox proportional hazards model, with the HR and 95% CI reported.

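### The primary win ratio counts cardiovascular hospitalizations in Section 6.1 but all-cause hospitalizations in the abstract and sample size, so the stated 90% power does not belong to the endpoint as defined

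*Protocol article*

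**What the plan says.** Four places in the protocol article describe the second tier, below all-cause death:

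| Place | Wording | Cause |
|---|---|---|
| Abstract, Methods | "including all‐cause deaths and the frequency of all‐cause hospitalizations" | all-cause |
| 6.1 Primary Efficacy Endpoint | "the number of non‐fatal cardiovascular hospitalizations from randomization to Week 84" | cardiovascular |
| 7 Sample Size Calculation | "The win ratio test incorporates both all‐cause mortality and all‐cause hospitalizations" | all-cause |
| 9.4 Statistical Methods | "combines time to all‐cause death and the frequency of nonfatal hospitalizations" | not stated |

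Section 7 names all-cause a second time in its planning effects: "HR 0.90 for all‐cause death and HR 0.70 for all‐cause hospitalization". These go with 90% power, 5% attrition and 838 participants, 419 per arm. No control event rates are printed; the scenarios are in Supporting Information Material 4, which is not at hand.

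**The concern.** A win ratio compares patients pair by pair on a fixed hierarchy. Pairs not decided on death pass to the second tier, so the definition of that tier largely determines which pairs are won, lost or tied. An admission for pneumonia or a fracture decides a pair under the all-cause rule and counts for nothing under the cardiovascular rule. The four passages therefore do not describe one primary hypothesis test.

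The power statement has the same fault. It was worked out for the broader outcome, while the section that defines the endpoint names the narrower one. Cardiovascular admissions are a subset of all admissions, so they cannot be more frequent, and fewer events leave more ties. Readers of the eventual result need to know which outcome was tested and whether the trial was sized for it.

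**Working it through.** **Inputs from the article.** Hazard ratios 0.90 (death) and 0.70 (all-cause hospitalization); 838 participants, 1:1; attrition 5%; 84 weeks; power 90%. Section 7 prints alpha as "0.05% and 5% expected attrition"; I use two-sided 0.05, the level in Section 9.4.

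**Assumed, because not given.** Control death risk by week 84: 1% to 8%. Cardiovascular share of hospitalizations: 80%, 50% or 30%. Cardiovascular hazard ratio: 0.70 or 0.50.

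**Step 1: the plan's own figure.** Evaluable patients are 838 × 0.95 = 796, or 398 per arm. The 90% cannot be reproduced without control rates. I therefore solved for the control hospitalization rate at which 838 gives exactly 90% for the all-cause endpoint.

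**Step 2: formula.** Let W and L be the probabilities that the treated patient of a random pair wins or loses, with death compared first and hospitalization second. Then WR = W/L. With h = (a patient's chance of a treated win)/W − (chance of a treated loss)/L, Var(ln WR) = [Var(h, treated) + Var(h, control)]/398, and power = Φ(ln WR/SE − 1.960).

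**Step 3: one case in full** (Poisson counts, 2% control death risk).
- All-cause: a control mean of 0.587 hospitalizations per patient gives W = 0.335, L = 0.219, WR = 1.529, SE = 0.131. Power = Φ(0.425/0.131 − 1.960) = Φ(1.28) = 90%.
- Cardiovascular at a 50% share, hazard ratio still 0.70: control mean 0.587 × 0.5 = 0.294, W = 0.225, L = 0.155, WR = 1.451, SE = 0.161. Power = Φ(0.372/0.161 − 1.960) = Φ(0.35) = 63%.
- Same share, hazard ratio 0.50: power 98%.

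**Step 4: all cases**, over death risks of 1% to 8%. The second column is the control risk of at least one hospitalization that makes 838 give 90% for all-cause.

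| Second-tier model | Risk needed | Power at 80% / 50% / 30% share, HR 0.70 | Power at 50% / 30% share, HR 0.50 |
|---|---|---|---|
| Poisson count | 43-51% | 83% / 63-64% / 43-44% | 97-98% / 83-88% |
| Time to first event | 51-61% | 85-86% / 70-72% / 50-53% | 99% / 92-93% |
| Over-dispersed count (negative binomial, dispersion 1) | 60-72% | 87-88% / 79-82% / 66-71% | above 99% / 99% |

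So with hazard ratio 0.70 carried over, power is below 90% at every share tested. With 0.50 it is above 90% at a 50% share under all three models, and at a 30% share it can fall on either side.

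**The case against.** The strongest reply is that narrowing the endpoint need not cost power. All-cause admissions include many that the intervention may not affect, so a stronger effect on cardiovascular admissions is plausible. Section 7 itself cites a 59% reduction in cardiovascular events as motivation. This stands. A reader might infer from the contradiction that the trial is underpowered for 6.1, but that needs the 0.70 to carry over unchanged, and the article does not say that it does. The rates behind the 838 are also unseen, and Section 7 claims adequate power over several scenarios rather than exactly 90% in one.

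A second reply is that the analysis plan, which Section 9.4 says was written before enrolment, may already settle the definition. It may, so a reader should not infer that the choice is open to be made once events are known. But such a plan can agree with only one of the printed definitions, and the article would still be wrong in the other places.

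Two further inferences are not supported. Section 8 lists the data management team neither among those kept unaware of allocation nor among those aware of it, so its central review cannot be called unblinded. And planning with hazard ratios while analysing a count is a separate matter that neither causes nor worsens this mismatch.

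Nothing in the article reconciles 6.1 with the abstract and Section 7. The motivating figures in Section 7 concern cardiovascular mortality, cardiovascular events and heart-failure hospitalization, so they do not show which definition was meant.

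**Conclusion.** The contradiction is real, stands in current text and concerns the primary endpoint. The only hospitalization effect used for planning is all-cause, so the 90% power was not derived for the endpoint that 6.1 defines. That conclusion holds whatever the cardiovascular rate or effect.

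The size of any power change is conditional. Taking 838 as exactly 90% for all-cause and 0.70 for cardiovascular admissions, power is about 83-88%, 63-82% or 43-71% at assumed shares of 80%, 50% or 30%, depending on the second-tier model and death risk. With an assumed 0.50 it is 97% or more at a 50% share and about 83-99% at 30%. Underpowering is therefore not shown; what is shown is that the power for 6.1 is unstated.

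**What to change.** Use one second-tier definition in the abstract, 6.1, Section 7 and 9.4.

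- **If all-cause is kept, as powered:** change 6.1 and 9.4 to the number of non-fatal all-cause hospitalizations, and report cardiovascular hospitalization as a secondary endpoint. This is a wording amendment with no extra patients. The downside is an outcome less specific to the intervention.
- **If cardiovascular is intended:** change the abstract, Section 7 and 9.4 to match. Recompute and state in Section 7 the control rate, effect size and power for cardiovascular hospitalization, in place of the all-cause 90% figure. The cost is a rerun of the power calculation; whether 838 is still enough depends on its result.

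The analysis plan should carry the same definition.

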TAMIS‐IA is a non‐commercial digital health platform developed collaboratively by academic and public institutions for research and service improvement. The platform's software and algorithms are maintained under institutional ownership, with no private licensing, profit generation, or commercial partnerships.

All members of the study team involved in follow‐up and data collection underwent structured and standardized training prior to participant contact. The training program included protocol‐based lifestyle counseling focused on weight management, physical activity, sodium reduction, alcohol moderation, and smoking cessation; application of guideline‐directed pharmacologic algorithms for hypertension, diabetes, and dyslipidemia; documentation procedures and data entry within the TAMIS‐IA platform; standardized telephone communication techniques; and identification and reporting of adverse events. Training was delivered by supervising physicians and senior investigators with expertise in cardiovascular and metabolic disease management. Preparatory training sessions were conducted regularly over the year preceding trial initiation through weekly 60‐min meetings focused on protocol familiarization, case discussions, and workflow standardization. Completion of formal training in international GCP, in accordance with International Council for Harmonization (ICH) guidelines, was a prerequisite for participation in study‐related activities. Competency was verified before participant interaction, and ongoing supervision is maintained throughout the trial to ensure protocol adherence and clinical safety.

Data monitoring will be performed remotely by the coordinating center, which maintains a full audit trail of user access, data entry, and edits. Automated consistency checks and range validations are integrated into the electronic data capture platform, and all queries or discrepancies are reviewed and resolved centrally before database lock to ensure data integrity.

Safety assessments are described in Supporting Information Material 3, including the classification, documentation, and reporting of adverse events.

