## Blinding

8

This study will be conducted as an open‐label trial. However, certain personnel will remain blinded to the randomization process. Specifically, the study sponsor, the independent Data Safety Monitoring Board (DSMB), study administrators, and personnel at the supporting organizations and vendors will be unaware of the allocation sequence.

All study data will be collected at participating sites and entered into the TAMIS‐IA platform, a secure, web‐based electronic data capture platform. Participants will be de‐identified using unique alphanumeric codes, and all data will be managed in compliance with the Brazilian LGPD. Data accuracy will be ensured through double‐entry verification, real‐time audit trails, and predefined data validation rules. Quality assurance activities will include biweekly remote audits, centralized query resolution, and continuous oversight by the Coordinating Center.

An independent DSMB composed of experts in cardiology, clinical trials, epidemiology, and biostatistics will oversee the study's safety and scientific integrity. The DSMB will remain blinded to treatment allocation and will conduct closed‐session interim reviews every 12 weeks, evaluating unblinded data for cumulative adverse events, recruitment metrics, and overall risk‐benefit profile. Predefined stopping criteria for harm, futility, or overwhelming efficacy will guide DSMB recommendations.

On the other hand, patients, study investigators, monitors, and clinical staff at the Health care Units will be aware of the allocation. To mitigate biases, the dataset will be de‐identified after data lock, ensuring that the study medication and treatment allocation are concealed from data analysts and statisticians.

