Access as a determinant of treatment effectiveness was demonstrated by the BARBER‐1 trial, which showed an improvement in hypertension control when care was delivered in community‐based settings routinely accessed by patients. In that study, barbershops functioned as sites for monitoring and referral, reversing the conventional model in which patients are required to seek out health services [20]. Similarly, the TAMIS platform integrates clinical decision support, remote monitoring, and technology‐mediated communication into the patient's environment, increasing access, reducing friction with the system, and enabling therapeutic adjustments.

This study has inherent limitations related to its open‐label design, including the risk of ascertainment bias in both clinical and self‐reported outcomes. Additionally, potential loss to follow‐up exceeding the estimated 5% may introduce attrition bias, thereby compromising internal validity and reducing the statistical power of the analysis. These factors should be considered when interpreting the results, despite the methodological strategies implemented to mitigate their impact.

The study aims to improve patient education, facilitate collaboration between primary care providers and specialists, and promote a more flexible, convenient, and cost‐effective health care model, ultimately leading to better patient outcomes.

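### If the primary endpoint keeps cardiovascular hospitalizations, the protocol describes no masking of the event review that would support its statement that ascertainment bias is minimized

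*Protocol article*

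**What the plan says.** Section 6.1 (Primary Efficacy Endpoint) ranks all-cause death first and then "the number of non‐fatal cardiovascular hospitalizations from randomization to Week 84". Events come from electronic records, discharge summaries and death certificates and "will undergo centralized review by the data management team to ensure accuracy and completeness across sites". It concludes: "The objectivity of these outcomes, combined with centralized validation procedures, minimizes the potential for ascertainment bias".

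On timing, Section 5 (Interventions) says that "all queries or discrepancies are reviewed and resolved centrally before database lock to ensure data integrity". Section 8 (Blinding) says "the dataset will be de‐identified after data lock", "ensuring that the study medication and treatment allocation are concealed from data analysts and statisticians"; Section 9.3 repeats that the groups are masked for analysts at that stage. Section 8 also lists several bodies that do not know the allocation sequence, and the participants and site-level staff who know the arm. The data management team is on neither list. The same section puts all study data into TAMIS-IA, which Section 5 describes as the tool that supports the intervention and whose decision support control participants do not get.

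The hospitalization tier is described differently elsewhere. The abstract and Section 7 (Sample Size Calculation) say all-cause, and Section 9.4 (Statistical Methods) says nonfatal hospitalizations without naming a cause. The Discussion lists among the limits of the open-label design "including the risk of ascertainment bias in both clinical and" self-reported outcomes.

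**The concern.** All-cause death needs no judgement on cause. A cardiovascular hospitalization does: an admission for breathlessness, syncope or renal decline in a person with diabetes can be called either way. Central review makes such calls consistent across sites. It makes them independent of arm only if the reviewer cannot tell the arm. The article gives central review as a reason why bias is minimized, yet the only masking of data that it describes starts after lock and protects a different group.

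If admissions in the remote-care arm were called cardiovascular slightly less often, the win ratio would move in favour of the intervention with no true effect. The opposite tendency would hide a real effect. Judgements made with the arm in view cannot be masked afterwards, so the matter has to be settled before review starts.

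**Working it through.** **1. The text side by side**

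| Question | What the article fixes |
|---|---|
| Does the second tier need a cause? | Yes in 6.1; no in the abstract and Section 7; not stated in 9.4 |
| Who reviews events? | Data management team (6.1) |
| Is that review masked? | Not stated |
| When is it done? | Not stated for events; queries and discrepancies are settled before lock (Section 5) |
| When is allocation concealed in the data? | After lock (8, 9.3) |
| From whom? | Analysts and statisticians |
| Could records show the arm? | Possible: data capture and intervention share one platform (5, 8) |

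Not knowing the allocation sequence (Section 8) protects concealment before randomization. It does not hide a participant's arm at event review.

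**2. The plan's own figure**

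The plan gives no figure for this bias. Its sample size of 838 allows 5% attrition: 838 × 0.95 = 796.1, so about 398 evaluable per arm; in reverse, 796 / 0.95 = 837.9, rounded up to 838. The power behind 838 cannot be reproduced, because the baseline event rates are in Supporting Information Material 4, which is not shown.

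**3. Illustration of size**

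From the article: 398 per arm, 84 weeks (about 1.61 years), death time ranked before number of hospitalizations, two-sided alpha 0.05 (Section 9.4).

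Assumed: no true effect; 5% deaths; 0.1, 0.2 or 0.3 cardiovascular hospitalizations per patient-year; either no variation in rate between patients or gamma frailty with variance 1. The share of patients with at least one event, ignoring deaths, is 1 − exp(−1.61 × rate) = 15%, 28%, 38% without frailty, and 1 − 1/(1 + 1.61 × rate) = 14%, 24%, 33% with it.

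Bias is imposed by multiplying the intervention-arm hospitalization rate by 1 − f. The test is z = log(win ratio) / SE with the U-statistic variance, in 2,000 simulated trials per cell.

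| Rate per year | Frailty variance | Type I error, f = 0 | f = 10%: win ratio, type I error | f = 20%: win ratio, type I error |
|---|---|---|---|---|
| 0.1 | 0 | 5.0% | 1.08, 7.2% | 1.18, 14.6% |
| 0.2 | 0 | 4.6% | 1.10, 9.7% | 1.22, 27.3% |
| 0.3 | 0 | 5.0% | 1.11, 12.9% | 1.25, 39.3% |
| 0.1 | 1 | 4.8% | 1.08, 7.4% | 1.16, 12.6% |
| 0.2 | 1 | 4.8% | 1.08, 8.4% | 1.19, 21.6% |
| 0.3 | 1 | 5.0% | 1.09, 10.8% | 1.20, 28.2% |

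With f = 5% the type I error is about 5–8%.

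**4. Why a simpler calculation should not be used**

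Comparing two proportions, p against p(1 − f), with 398 per arm gives 9%, 11% and 16% for f = 10% at p = 15%, 20% and 30%, and 24%, 31% and 48% for f = 20%. This ignores the death tier and the ties. Win-ratio simulations at the same proportions give about 7–13% and 15–31%, so the two-proportion figures are too high for this endpoint.

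**The case against.** The strongest reply is that the exposure is inferred. Section 6.1 gives no date for the event review, and the sentence in Section 5 on work before lock covers only queries and discrepancies. Nothing says that the data management team sees the arm or assigns cause; its stated task is a check of accuracy and completeness. Access rights may be set out in Supporting Information Material 2 or the full protocol. All of this stands. A reader might infer that reviewers classify events before lock with the arm in view; the documents do not say so, and the point claims only that nothing described prevents it.

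Second, the tier may be meant as all-cause, as the sample size assumes. Cause attribution then drops out and mainly the detection of events remains exposed. This also stands, and makes the point conditional.

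Third, a condensed article may leave masking of event review to the full protocol. Silence alone would be no finding. Here, however, the article names the reviewer, says when and for whom allocation is concealed, and asserts that bias is thereby minimized. That assertion is what lacks support.

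Fourth, the Discussion already concedes the risk. Minimized bias and some residual risk are not strictly contradictory, but the concession does not supply the missing safeguard.

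A reader might also suppose that hospitalization decides most pairs. With 15–30% of patients hospitalized and 5% deaths, it decides about 21–40% of all pairs in simulation. It does decide most of the pairs that are decided at all.

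**Conclusion.** The point holds in conditional form. If cardiovascular hospitalization is kept as the second tier, the safeguards described do not support the statement that ascertainment bias is minimized, and attribution that differs by arm is possible. The documents do not show that such bias occurs or that reviewers know the arm.

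On size, 10% relative under-calling in the intervention arm takes type I error from about 5% to about 7–13%, with a null win ratio of 1.08–1.11. With 20% under-calling the figures are about 13–39% and 1.16–1.25. The event rates, the 5% death risk and the degree of under-calling are all assumptions; the article gives none of them. Under all-cause hospitalization this attribution route disappears. The change is worth making before event review begins.

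**What to change.** State one definition of the hospitalization tier in the abstract and Sections 6.1, 7 and 9.4. Then do one of the following.

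- Use all-cause non-fatal hospitalization, in line with the abstract and the sample size section. No cause attribution is then needed.
- Keep cardiovascular hospitalization and state in Section 6.1 that cause is classified under written criteria, from event packets stripped of arm, platform contacts and titration notes. One member of the existing data team redacts; a different member, without access to allocation, classifies. One person doing both would not be masked.

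If neither is adopted, delete the statement that bias is minimized, so that Section 6.1 agrees with the limitation in the Discussion.

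The cost is protocol wording and, under the second option, some clerical redaction per event and a separation of roles within the existing team. Participants undergo no new procedure.
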